#### Aim 2: Measure Differences in Inpatient and Outpatient Opioid Use and Postsurgical Health Care Utilization

Inpatient postoperative opioid use will be recorded for 3 inpatient calendar days before discharge in oral morphine equivalents (OME) per day. Outpatient opioid use and pain scores will be assessed through an 11-item questionnaire administered at 1-month follow-up. Hospital length of stay, number of days in an extended care facility, emergency room, urgent care, unplanned doctor office visits, and readmission will be recorded in a composite endpoint defined as total days spent at home within the first 30 days after surgery. We hypothesize that patients who receive a comfort coach consume less opioids after surgery and demonstrate lower postsurgical health care utilization.

##### Outcomes Measures for Aim 2

###### Opioid Use

Opioid amounts will be converted to OME [67]. Inpatient opioid use will be obtained through electronic chart review for the 3 inpatient calendar days before discharge (intravenous and oral) and will be reported daily in OME. Outpatient opioid use will be collected using the 11-item questionnaire administered at the 30-day postoperative clinic appointment and will be reported as total OME consumed postdischarge. Additional data captured through chart reviews and clinic questionnaires include the type of opioid, the amount prescribed (OME), number of refills, outpatient storage location, and opioid education received regarding risks and proper opioid disposal.

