###### Analytic Approach

Mean inpatient opioid use, prescription size, postdischarge opioid use (in OME), and mean postsurgical health care utilization days will all be compared between groups using two-tailed *t* tests. Individual health care utilization outcomes will also be compared separately with two-tailed *t* tests for continuous data and chi-square tests for categorical data.

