#### Aim 2: Measure Differences in Inpatient and Outpatient Opioid Use and Postsurgical Health Care Utilization

The role of surgery in the opioid epidemic has been well described [73] through widespread overprescribing [38,46], with the amount prescribed shown to be the most significant predictor of opioid consumption [47] and development of new persistent opioid use among previously opioid-naive surgical patients [74-81]. In cardiac surgery, persistent opioid use has been shown to confer higher rates of complications, length of stay, and health care costs [37]. Efforts have focused primarily on decreasing opioid prescription [72,82-85], whereas nonpharmacological interventions have not been well described in surgical patients. Comfort coaches may provide a nonpharmacological method for further decreasing opioid use, which would complement and enhance ongoing efforts to decrease prescribing. By addressing concurrent anxiety and decreasing perceived pain, nonpharmacological techniques may serve as valuable tools in addressing the opioid epidemic and improving surgical care.

The effect of the comfort coach’s interventions on anxiety, pain, stress, and opioid use can also be measured through overall health care utilization. As patient anxiety and pain decrease while satisfaction and comfort increase, we expect them to be better equipped and more prepared to leave the hospital. In addition, whereas individual nonpharmacological techniques such as preoperative educational prompts [48,49], massage therapy [50], and music [34] have been tested within hospital settings, no trial has measured the effect of an individualized comfort coach utilizing individualized nonpharmacological techniques throughout the entire perioperative course, from preoperative clinic visit through 90-days of postoperative follow-up. An innovative aspect of this trial is sending different nonpharmacological tools home with patients based on their individualized preferences and continuing self-administered nonpharmacological techniques for 30 days postoperatively. We expect these sustained efforts to reflect decreased health care utilization through hospital length of stay, minimized or eliminated days spent in an extended care facility, prevented emergency room, urgent care, and unplanned doctor office visits, telephone calls, and readmissions, all of which may decrease health care costs.

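### Inpatient opioid use is counted back from discharge, which the coach is expected to bring forward, so a true opioid reduction can be diluted

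*Protocol article*

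**What the plan says.** The inpatient window is fixed in two places in the protocol article. The opening of Aim 2 states: "Inpatient postoperative opioid use will be recorded for 3 inpatient calendar days before discharge in oral morphine equivalents (OME) per day". The Opioid Use section repeats it: "Inpatient opioid use will be obtained through electronic chart review for the 3 inpatient calendar days before discharge (intravenous and oral". Outpatient use comes from the 30-day questionnaire and "will be reported as total OME consumed postdischarge". No inpatient opioid measure counted from surgery is given.

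The Analytic Approach for Aim 2 states: "Mean inpatient opioid use, prescription size, postdischarge opioid use (in OME), and mean postsurgical health care utilization days will all be compared between groups". The method named there is a two-sided t test. The section does not align use to postoperative day or take account of length of stay. The Power Analysis lists inpatient and outpatient opioid use as secondary endpoints.

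The Aim 2 hypothesis is that "patients who receive a comfort coach consume less opioids after surgery and demonstrate lower postsurgical health care utilization". The Discussion of Aim 2 says of coached patients that "we expect them to be better equipped and more prepared to leave the hospital", and adds: "We expect these sustained efforts to reflect decreased health care utilization through hospital length of stay".

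**The concern.** The hypothesis is about opioid use after surgery, but the measuring window is set by discharge. Discharge is a post-randomization event, and the protocol expects the intervention to move it. If the coach shortens the stay, the last three inpatient days fall on different postoperative days in the two arms, and the t test compares unlike periods.

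If use declines as patients recover, the mismatch works against the coach. The plan is therefore most exposed when its own length-of-stay hypothesis is true, and a larger sample would not remove the bias. Opioid use is secondary, but it is part of the trial objective and half of Aim 2. It is also one of the two clinical examples used to check the sample size.

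**Working it through.** **1. The plan's own opioid figure.** The Power Analysis gives means of 200 and 140 OME, SDs of 125 and 100, 80% power, alpha .05 and a total of 114.
- Average SD = √((125² + 100²)/2) = 113.2.
- Normal approximation: 56 per arm, 112 in total. Noncentral t: 57 per arm, 114 in total, power 0.801.

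The stated 114 reproduces, so no sample-size figure is in question here.

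**2. Shift caused by the window.** The protocol gives neither a daily opioid trajectory nor a length of stay, so two inputs are assumed:
- r, the fraction by which daily OME falls per postoperative day, the same in both arms;
- s, the number of days by which coach discharge is earlier.

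Daily use is proportional to (1 − r)^day. Moving a 3-day window s days earlier multiplies its mean by (1 − r)^(−s). If use on each postoperative day is identical in the arms, that factor is the expected coach/control ratio:

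| r | s = 1 | s = 2 | s = 3 (upper bound) |
|---|---|---|---|
| 0% | 1.00 | 1.00 | 1.00 |
| 5% | 1.05 | 1.11 | 1.17 |
| 10% | 1.11 | 1.23 | 1.37 |
| 15% | 1.18 | 1.38 | 1.63 |
| 30% | 1.43 | 2.04 | 2.92 |

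The column s = 3 is an upper bound. The 3-day planning difference is in days at home, which also counts extended care, readmissions, emergency, urgent care and unplanned office visits.

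**3. With a true 30% reduction on every postoperative day.** The observed ratio is 0.70 × (1 − r)^(−s):

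| r | s = 1 | s = 2 | s = 3 |
|---|---|---|---|
| 0% | 0.70 | 0.70 | 0.70 |
| 5% | 0.74 | 0.78 | 0.82 |
| 10% | 0.78 | 0.86 | 0.96 |
| 15% | 0.82 | 0.97 | 1.14 |
| 30% | 1.00 | 1.43 | 2.04 |

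The reduction is fully cancelled when (1 − r)^s = 0.70, that is at r = 30% for s = 1, 16% for s = 2 and 11% for s = 3.

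**4. Effect on power.** This step applies the planning means and SDs to the pre-discharge measure. That is a further assumption, because the window behind the 200 OME is not stated. With 57 per arm, SE = √((125² + 100²)/57) = 21.2. Using the normal approximation:
- no shift: difference 60, power 0.81;
- r = 5%, s = 1: coach mean 140/0.95 = 147.4, difference 52.6, power 0.70;
- r = 10%, s = 1: coach mean 140/0.90 = 155.6, difference 44.4, power 0.55;
- r = 10%, s = 2: coach mean 140/0.81 = 172.8, difference 27.2, power 0.25.

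**5. Does the postdischarge total compensate?** Let q = 1 − r, let controls leave on day D, and let follow-up end at day 30. The postdischarge total is then proportional to q^D − q^30. The coach/control ratio is (q^(D−s) − q^30)/(q^D − q^30), which exceeds q^(−s). The shift has the same direction as in step 2. Even with flat use, the coach window is longer, by (30 − D + s)/(30 − D).

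Adding the two measures does not help either. Inpatient days before the 3-day window are never counted, so the sum covers 3 + (30 − D) days in one arm and 3 + (30 − D + s) in the other.

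**The case against.** The strongest case against is that the size of the bias rests entirely on assumed inputs. It is zero for the inpatient measure if use is flat or if the coach does not change the stay. At modest values (5% to 10% per day, one day) it is only 5% to 11%. The scenario of identical daily use is also not the protocol's own mechanism, which expects earlier discharge because pain and anxiety fall. All of this stands. It is why step 3 matters more than step 2: under the protocol's own mechanism the usual result is a diluted reduction.

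The endpoint is secondary and the primary endpoint is untouched. Inpatient use is reported by day, and individual utilization outcomes are compared separately, so a difference in stay should be visible. This stands in part. Visibility helps interpretation, but the opioid days before the window are not collected, so the arms cannot be fully realigned afterwards.

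Pre-discharge use may also be of interest in its own right, next to prescription size and use at home. The protocol does not give that reason, but it is a fair ground for keeping the measure.

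Three stronger readings might be inferred, and the protocol does not support them:
- That a shorter stay necessarily makes coached patients look like heavier users. With a 30% reduction present, this needs a steep decline, a large change in stay, or both.
- That the bias is 63% to 192%. Those figures take s = 3 with daily falls of 15% to 30%, and so load the whole days-at-home difference onto length of stay.
- That the window usually misses the coach visits at extubation and chest tube removal. The protocol gives no timing for either event relative to discharge.

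**Conclusion.** The point holds in a limited form. As written, the plan compares inpatient opioid use on different postoperative days if the coach shortens the stay, as the protocol expects. If use declines with time since surgery, the comparison is biased against the coach. The likely result is dilution of a true reduction; cancellation or reversal needs the more extreme combinations. For a stay one day shorter, the distorting factor runs from 1.00 (flat use) through 1.05, 1.11 and 1.18 to 1.43 (30% fall per day). The postdischarge total does not correct it.

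The conclusion rests on two conditions that the protocol cannot confirm: a declining daily trajectory and an actual difference in stay. It concerns a secondary endpoint and leaves both the primary endpoint and the sample-size figures as they are. It is worth correcting because the correction is cheap, but it does not threaten the trial.

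**What to change.** Before the analysis, abstract inpatient opioid administrations from surgery onward, from the same electronic chart already under review. Make the between-arm inpatient comparison on OME over fixed postoperative days, for example days 1 to 3, where the shift factor is 1.00. Choose days on which nearly all patients are still in hospital.

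Supplement this with total OME from surgery to day 30, combining all inpatient administrations with questionnaire-reported postdischarge use. State that the second part relies on recall and is missing when the questionnaire is missing; the protocol plans for 20% missingness.

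Keep the 3-day pre-discharge measure and the postdischarge total as reported measures, interpreted alongside length of stay by arm. This preserves the separate inpatient and outpatient description that Aim 2 calls for.

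The cost is extra chart abstraction for about 154 patients. No further patient contact is needed, and having 144 patients already enrolled is no obstacle.

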###### Postsurgical Health Care Utilization

The primary endpoint of this trial is a composite outcome defined as the total number of days spent at home within the first 30 days after surgery. Each partial or full day spent in the hospital (during index or readmission hospitalization), at any extended care facility, emergency room, urgent care center, or doctor’s office for an unplanned visit will be subtracted from 30 to generate the total number of full days spent at home. This number will reflect total health care utilization within the immediate postoperative period, with lower values indicating more utilization. The number of days in an extended care facility, outside hospital emergency room or urgent care visits, and readmissions are routinely discussed at the 30-day postoperative clinic appointment and will be captured through a combination of chart review by 2 study team members and conversations with patients. In addition, the number of telephone calls made by each patient or patient’s family member to the University of Michigan hospital system regarding the clinical concerns of the patient within the first 30 postoperative days will be captured through chart review and independently verified by 2 study team members. If necessary, we will then use Michigan Value Collaborative data to quantify differences in health care utilization by comparing total and component 90-day episode payments among Medicare, Blue Cross Blue Shield of Michigan, and Medicaid beneficiaries, as our team has previously done in both coronary artery bypass (CABG) [31] and aortic valve replacement [30] studies in Michigan.

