**Methods:**

To address these aims, we will perform a prospective, randomized controlled trial of 154 adult cardiac surgery patients at Michigan Medicine. Opioid-naive patients undergoing first-time, elective cardiac surgery via sternotomy will be randomized to undergo targeted interventions from a *comfort coach* (intervention) versus usual care (control). The individualized *comfort coach* interventions will be administered at 6 points: preoperative outpatient clinic, preoperative care unit on the day of surgery, extubation, chest tube removal, hospital discharge, and 30-day clinic follow-up. To address aim 1, we will examine the effect of a *comfort coach* on perioperative anxiety, self-reported pain, functional status, and patient satisfaction through validated surveys administered at preoperative outpatient clinic, discharge, 30-day follow-up, and 90-day follow-up. For aim 2, we will record inpatient opioid use and collect postdischarge opioid use and pain-related outcomes through an 11-item questionnaire administered at the 30-day follow-up. Hospital length of stay, readmission, number of days in an extended care facility, emergency room, urgent care, and an unplanned doctor’s office visit will be recorded as the primary composite endpoint defined as total days spent at home within the first 30 days after surgery. For aim 3, we will perform semistructured interviews with patients in the intervention arm to understand the *comfort coach* intervention through a thematic analysis.

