### Patient Enrollment and Randomization

Cardiac surgical patients will be recruited from the Frankel Cardiovascular Center (FCVC) at Michigan Medicine. Opioid-naive patients undergoing first-time, elective cardiac surgery through a full median or miniature sternotomy beginning September 3, 2019, were screened for a targeted enrollment of 154 patients for randomization. Approximately 600 to 750 patients meeting these criteria underwent surgery at Michigan Medicine in 2017. Opioid-naive is defined as opioid-free at the time of preoperative clinic history and physical examination.

Patients lost to follow-up will be censored for data analysis, and missing individual intervention points will be dealt with by multiple imputations, as appropriate. We will compare the clinical and sociodemographic attributes of patients who decline participation and patients lost to follow-up with those of patients with complete follow-up to assess potential responder bias. We estimated a 20% rate of missingness, which was incorporated into our power calculation. On the basis of historical institutional data, we anticipated approaching 5 to 10 patients per week for potential enrollment, with an approximate 5 to 7 month enrollment period within a 12-month study period for completion of clinical follow-up, data analysis, and manuscript production. Although this timeline was affected by the COVID-19 pandemic forcing a pause in enrollment between March 14th and the time of writing, we were 93.5% (144/154) enrolled at the time of pausing and remained optimistic about completing enrollment within our 12-month study period. We used block randomization with randomly variable block sizes generated with Stata 15 software (StataCorp LLC, College Station, TX) and computer randomization occurred with the treatment assignment tool (Treatment Assignment Tool-University of Michigan [TATUM]) from the Michigan Institute for Clinical and Health Research.

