##### Power Analysis

Our primary endpoint is composite of health care utilization, defined as the total number of days spent at home within the first 30 days after surgery. Secondary endpoints include mean GAD-7 and PHQ-9, KCCQ-12, Picker Patient Experience Questionnaire, IES-R, and Brief Pain Inventory Scores and mean inpatient and outpatient opioid use.

We will compare mean days with a two-tailed *t* test and set the power of this study at 80% with alpha (Type I error) of .05 and the Cohen *d* effect size (defined as the difference in means divided by standard deviation) between medium (0.5) and large (0.8) [69,70], which yields a minimum sample size of 52 patients to detect a large effect size and 128 to detect a medium effect size [71]. Incorporating 20% missingness, a sample size of 154 patients will adequately detect a medium effect size. We next verified this statistically derived sample size with clinically relevant examples. Although most large series reporting opioid use report the median and interquartile range of OME [47,72], our sample size should be sufficient to satisfy the central limit theorem and use mean values. At our institution, the mean opioid use after sternotomy in 2017 was 200 OMEs. We estimated that to detect a 30% reduction in opioid use (mean 140 OMEs) with a standard deviation of 125 OME in the control and 100 OME in the intervention arms, a sample size of 114 would be required. For composite health care utilization, demonstrating a 3-day difference between the arms with a 6-day standard deviation would detect by a total sample size of 128 patients. With 154 patients, we should have adequate power to detect a difference in our primary outcomes for aims 1 and 2.

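### The primary-endpoint formula (30 minus facility days) makes no deduction for days after death, so an early in-hospital death outscores an uncomplicated recovery

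*Protocol article*

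**What the plan says.** The Postsurgical Health Care Utilization section of the protocol article calls the primary endpoint a "composite outcome defined as the total number of days spent at home within the first 30 days after surgery". The Abstract and the Power Analysis section use the same label.

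The same section then gives the arithmetic. The deductions start with "Each partial or full day spent in the hospital (during index or readmission hospitalization), at any extended care facility, emergency room, urgent care center" and end with unplanned visits to a doctor's office. These days "will be subtracted from 30 to generate the total number of full days spent at home". The starting value is 30 for every patient. The section describes the result as a measure of utilization, "with lower values indicating more utilization".

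Death is not among the deductions, and the article states no score for a patient who dies. The nearest rule is in Patient Enrollment and Randomization: "Patients lost to follow-up will be censored for data analysis". It does not mention death.

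The Power Analysis section plans a two-sided t test on mean days. It bases the sample size on a 3-day difference, a 6-day standard deviation and 128 patients in total.

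**The concern.** The label and the formula disagree for any patient who dies within the window. Someone who dies in hospital has spent no day at home, yet the formula credits every day after death as a day at home. The earlier the death, the better the score.

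This is more than a gap in the description. The article fixes a starting value and names the deductions, and those instructions return a wrong value for the most serious outcome. An analysis program written from them would put early deaths near the top of the scale on which the arms are compared.

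**Working it through.** **Inputs from the article.** Starting value 30; facility days deducted; difference 3 days; SD 6 days; two-sided alpha 0.05; power 80%; total 128 evaluable and 154 randomized.

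**Assumptions, not in the article.** Allocation 1:1, so 154/2 = 77 per arm. Where needed: 30-day mortality of 0.5% to 3%, and a mean of 22 days with SD 6 among survivors.

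**1. The plan's own figure.** d = 3/6 = 0.5. A two-sample t test needs 63.77, so 64 per arm and 128 in total, with power 80.1%. The stated 128 is reproduced.

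**2. The formula applied to deaths.** For a death during the index stay on day D, the score is 30 − D.

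| Day of in-hospital death | Score as written | Score if days after death are also deducted |
|---|---|---|
| 1 | 29 | 0 |
| 3 | 27 | 0 |
| 5 | 25 | 0 |
| 10 | 20 | 0 |
| 14 | 16 | 0 |
| 20 | 10 | 0 |

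A survivor discharged on day 7 with no further care scores 30 − 7 = 23. Any in-hospital death before day 7 therefore outscores that patient. Counting the day of surgery differently shifts both scores equally and leaves the order unchanged.

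**3. Effect on an arm mean.** Each day-5 death scored 25 instead of 0 adds 25/77 = 0.32 day, and 0.32/3 = 11% of the target difference. With 64 evaluable per arm it adds 25/64 = 0.39 day (13%). A net excess of two such deaths in one arm adds 50/77 = 0.65 day (22%), and of three, 75/77 = 0.97 day (32%).

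**4. How likely an imbalance is.** This treats deaths as binomial with equal risk in both arms and 77 per arm.

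| Assumed 30-day mortality | Expected deaths in 154 | P(arms differ by 0 or 1 death) | P(arms differ by 3 or more) |
|---|---|---|---|
| 0.5% | 0.8 | 92% | 1% |
| 1% | 1.5 | 80% | 4% |
| 2% | 3.1 | 63% | 14% |
| 3% | 4.6 | 54% | 23% |

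**5. Cost of scoring deaths as 0.** With mortality p, variance = (1 − p) × 36 + p(1 − p) × 22².

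- p = 1%: 35.64 + 4.79 = 40.43, so SD = 6.36. Power for 3 days at 64 per arm is 75%.
- p = 2%: 35.28 + 9.49 = 44.77, so SD = 6.69. Power is 71%.

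Keeping the first term at 36 gives SD 6.39 and 6.74, and power 75% and 70%.

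**The case against.** **The article is condensed.** The scoring of deaths could sit in a full protocol or SAP that is not shown. That would answer a complaint that a rule is missing. It does not answer a stated formula that gives a wrong score: a SAP that follows it inherits the error, and one that departs from it changes the published endpoint.

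**The score is meant to measure utilization, not survival.** This has force. The article ties low values to more utilization, and its hypotheses do not include mortality. Bringing death into the score therefore changes what is estimated. But the endpoint is also named as days at home, and the formula contradicts that name. Low utilization because the patient died is not the benefit the article describes in its Discussion, where patients are expected to be readier to leave hospital.

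**Equal mortality means no expected bias.** This stands. Nothing in the article suggests that the coach affects mortality. If the number and timing of deaths have the same distribution in both arms, the misscoring adds the same expected amount to each. A reader might infer a systematic bias, or take the 0.97-day figure as typical; neither is supported. That figure needs a net excess of three deaths around day 5 in one arm, which is improbable at low mortality. Late in-hospital deaths already score low.

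**The censoring rule.** A reader might infer that it would remove deaths from the analysis. The article does not class deaths as lost to follow-up, so this is only a possible reading. It is a reason to exclude that reading explicitly.

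**Conclusion.** The point holds. The formula contradicts the endpoint's label and ranks an early in-hospital death above an ordinary recovery, and no other section of the article corrects this. That conclusion rests on the text and needs no assumption about mortality.

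The size does depend on assumptions. Each day-5 death moves its arm mean by about 0.32 day at 77 per arm, or 11% of the 3-day target. The comparison is distorted only when early deaths are unequal in number or timing, and then in favour of the arm with more of them. With few or no deaths, the numerical effect may be negligible. The documents do not show that the trial result will be biased, only that the primary score is wrong for these patients. Because the correction is cheap and must not be chosen once deaths by arm are known, it should be made before analysis.

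**What to change.** Before the quantitative analysis, redefine the primary endpoint as days alive and at home to day 30, with one prespecified rule for deaths. For example, death within 30 days scores 0. State that deaths are not handled under the rule for patients lost to follow-up.

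Report the alternative, deducting only the days after death, as a sensitivity analysis. The two rules must not be merged. They agree at 0 for a death during the index stay but differ after discharge: a patient discharged on day 7 who dies at home on day 25 scores 0 under the first and 17 or 18 under the second, depending on whether the day of death counts.

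**Cost.** The trial is registered and 144 of 154 patients were enrolled at the time of writing, so this needs a documented amendment as well as a change to the derivation program. Vital status at day 30 must be confirmed for every patient; the article does not say that its chart review collects this. Power at 128 evaluable may fall from 80% to about 75% at 1% mortality or 70% to 71% at 2%, under the assumptions above, unless the 6-day SD already includes deaths.
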